# 3. STUDY DESIGN AND METHODS

**3.1 Study design**

The study design is that of a randomised intervention study. Children with confirmed *P. falciparum* malaria, meeting all study inclusion criteria, will be enrolled in the study for a period of 28 days. Participants will be assigned at random to either the intervention or the control group.

The intervention group will receive treatment for malaria plus 1 bag of RUTF per day for 14 days. The control group will receive treatment for malaria without provision of RUTF.

Random allocation to either intervention or control group is thought to be acceptable by the population as RUTF is seen as a medicine rather than a food item. A similar study did not meet a problem with randomisation.[[18]](#footnote-2) For other illnesses, the participants will be offered medical treatment according to the best local standards.

Follow-up visits will be scheduled for directly observed treatment for malaria (day 0, 1 and 2), malaria parasite density and clearance (D0, D2, and until slide is negative; and for weight measurements at day 0, 1, 13 and 27. Weight will be measured twice at each visit by two independent observers. A detailed questionnaire will be conducted at the start, and at day 13 and 27.

All participants who attend follow up sessions at the clinic will receive a small incentive[[19]](#footnote-3)* in order to compensate for lost time due to participation in the study (RUTF will not be given to the control group at the end of the study).

The study will be conducted in the period (May-June) that is likely to have a stable prevalence of malnutrition, a stable incidence of *P. falciparum* malaria and other morbidities (e.g. pneumonia and diarrhoea). The total duration of the data collection will be 2 months for data gathering: 4 weeks of enrolment (40 participants per week) and 4 weeks of follow up (the last follow-up being done 4 weeks after the last enrolment).

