**3.3. Sampling frame**

The nature of the intervention means that blinding of health workers and participants is not possible. In order to address observer bias, the interviews will be carried out by field staff who are not part of the normal health services staff of the study clinics.

The sample size is based on the hypothesis that, compared to a control group of children who receive routine malaria treatment without nutritional supplementation, children receiving supplementation will show significantly greater average weight gain over the study period.

The following is the basic formula for calculating required sample size in each group (assuming equal numbers sampled in each group) for the difference between two population means[[20]](#footnote-4) :

n>2 ((z 2α σ)/d)2

Where:

n=number sampled in each population

d= difference in sample means

σ =standard deviation

Z2α = standardised normal deviate exceeded by specified probability

Assumptions for sample size calculations have been based on two previous studies from the Gambia assessing the impact of infection on weight gain. The first study, carried out in 1977, demonstrated that the incidence of either malaria or diarrhoea have a significant negative effect on weight gain.6 The second study, an intervention study published in 1996, demonstrated that short-term nutritional supplementation for diarrhoea had a significant impact on weight gain.10 This study provides the parameters for the sample size calculation, while the first study provides the basis on which we extrapolate the evidence that nutritional supplementation may address post-infection lack of weight gain related to diarrhoeal disease, to a similar impact on post-malaria weight gain. The primary sample size calculation is based on demonstrating a statistically significant difference in mean weight gain/loss between the intervention and control groups at two weeks.

# Expected mean change in weight for control and intervention groups are: 10

- Control group 0.09 kg/14 days (standard deviation 0.44)

- Intervention group 0.44 kg/14 days (standard deviation 0.33)

(For all calculations, power of 80% and 5% level of significance for a two- sided test of hypothesis was used. The Z2α would be in this case1.96)

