**4.2 Outcome parameters:**

**Main outcome:**

Average weight gain (g/kg/day) in the intervention group from day 1 to day 14 will be compared with the average weight gain in the control group.

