**7.3 Weight changes**

Weight gain is defined as the difference in weight between weight on day one and weight on day 14. The weight of an individual varies during the day and therefore ideally weight should be measured at the same time of the day on each follow up visit. As patients may initially present at any hour during the day, their enrolment in the study and the first weight taken will be at any time on this day (day 0). In order to standardise the time of taking weight, to limit intra-day variation, patients will be asked to come back for follow up within a certain period in the day (pre or post meal times). The follow up visits will be scheduled at the same period of the day. The weight at day 1 (the day after enrolment) will be used as baseline.

Weight changes in a short period are very small. Therefore even a small degree of measurement error could influence outcomes. By weighing each individual twice with two independent observers, measurement error will be calculated and the average will be taken for the analysis. Electronic weighing scales will be used (SECA 834 and 835) that have a precision of >=20g.

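### Section 7.3 averages the two weighings with no maximum allowed difference and no re-weigh, so half of any gross misread stays in that child's weight change

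*Protocol*

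**What the plan says.** Section 3.1 fixes duplicate weighing: "Weight will be measured twice at each visit by two independent observers". Section 7.3 gives the handling rule for the two readings: "measurement error will be calculated and the average will be taken for the analysis". The same section warns that two-week weight changes are small and that even minor measurement error could affect the results. It names two electronic scale models, "that have a precision of >=20g".

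The main outcome in section 4.2 is built on these weights: "Average weight gain (g/kg/day) in the intervention group from day 1 to day 14 will be compared with the average weight gain in the control". A secondary outcome there is the proportion of children who lost weight in each group.

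Other quality controls exist. Staff are trained in weighing (7.2). A research supervisor evaluates procedures, observes a sample of them and has records checked at random (7.1). Data are entered twice (section 10). None of these compares the two weights at the visit or triggers a further weighing. For blood slides, by contrast, section 7.5 does require the two microscopists to resolve discrepant readings.

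**The concern.** Two weighings of the same child at one visit on an electronic scale should agree closely. A large gap means that at least one reading is wrong, for example through a wrong digit, a moving child or a slip in writing the number down. The second observer makes such an error visible at the one moment when it can be put right. A rule that only calculates the error and averages does not use that opportunity: the mean keeps half of the error, and a summary of measurement error across children corrects no individual weight.

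This is a procedure at the scale, so a later analysis plan cannot supply it. With only two readings left, an analyst often cannot tell which one is wrong. At stake are the precision of the main outcome and the classification of children as having gained or lost weight.

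**Working it through.** **Inputs from Protocol section 3.3.** "Control group 0.09 kg/14 days (standard deviation 0.44" kg); "Intervention group 0.44 kg/14 days (standard deviation 0.33" kg); "power of 80% and 5% level of significance for a two- sided test of hypothesis was used". Proposed size: 100 per group. Loss to follow-up: 20%, which leaves 100 × 0.8 = 80.

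**The plan's own figure.** Planned difference: 0.44 − 0.09 = 0.35 kg. Summed variance: 0.44² + 0.33² = 0.1936 + 0.1089 = 0.3025 kg². Then n = (1.960 + 0.842)² × 0.3025 / 0.35² = 19.4, so 20 per group. This reproduces the protocol's 20.

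**One misread, one child.** An error e in one of the two readings at a visit leaves e/2 in that visit's mean, and so e/2 in the child's change.
- It exceeds the planned difference if e/2 > 0.35, that is e > 0.70 kg. A 1 kg misread leaves 0.50 kg; a 0.5 kg misread leaves 0.25 kg; a 0.1 kg misread leaves 0.05 kg.
- It turns the expected control gain into a loss if e/2 > 0.09, that is e > 0.18 kg, when the error is upward at baseline or downward at follow-up.

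**One misread, the arm mean.** The shift is e/(2n). For 1 kg and n = 100 it is 0.5/100 = 0.005 kg, or 0.005/0.35 = 1.4% of the planned difference.

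**Many misreads.** Assumption, not in the documents: each reading has probability p of a 1 kg error of random sign, equally in both arms. The change uses four readings, so the added variance per arm is 4 × p × 0.5² = p kg², and the summed variance becomes 0.3025 + 2p. The share of children with at least one affected reading is 1 − (1 − p)⁴. Power at 80 per group is Φ(0.35/√(summed variance/80) − 1.96). The detectable difference at 80% power is 2.802 × √(summed variance/80).

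| p | Children affected | Summed variance (kg²) | Rise | 100 per arm equivalent to | Required n | Power at 80 per arm | Detectable difference at 80 per arm |
|---|---|---|---|---|---|---|---|
| 0 | 0% | 0.3025 | – | 100 | 20 | 99.99% | 0.172 kg |
| 1% | 3.9% | 0.3225 | 6.6% | 94 | 21 | 99.98% | 0.178 kg |
| 2% | 7.8% | 0.3425 | 13.2% | 88 | 22 | 99.97% | 0.183 kg |
| 3% | 11.5% | 0.3625 | 19.8% | 83 | 24 | 99.94% | 0.189 kg |

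At 100 per arm, power is above 99.9% in every row.

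**Extreme errors.** If 2% of children had one 10 kg misread, the average standard deviation would rise from 0.389 to √(0.389² + 0.02 × 5²) = 0.81 kg, and power at 100 per group would be about 87%.

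**With a tolerance t.** If the other reading is correct, a misread that passes the check leaves at most t/2. For t = 0.1 kg that is 0.05 kg per visit, against 0.50 kg for an unchecked 1 kg misread.

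**The case against.** The strongest objection is that the trial's conclusion would hardly change. On the plan's own inputs 20 children per group suffice and 100 are planned, so even a 3% rate of 1 kg misreads leaves power for 0.35 kg at about 99.9%. The rate and size of the misreads are assumptions, and power falls materially only with errors near 10 kg. Duplicate weighing with averaging is itself a safeguard that halves any single error, and training, supervision and record checks stand beside it. Re-weigh tolerances often sit in a measurement procedure, and no tolerance can be derived from the documents. All of this stands and limits the weight of the point.

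It does not remove the point. None of the listed controls prompts a re-weigh, and double entry catches keying errors but not a wrong number written at the scale. The planned effect is also borrowed from a diarrhoea study that supplied 796 to 900 kcal/day, against 500 here (section 3.4), and section 3.3 itself expects more variation after malaria. Avoidable variance would matter more if the true effect were smaller.

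Three stronger readings are tempting, and the documents do not support them.
- A reader might infer that one misread puts an error larger than the planned effect into the trial result. The 0.35 kg is a difference between group means, and one 1 kg misread moves a mean of 100 by 0.005 kg.
- A reader might infer that the protocol orders averaging at any discrepancy. It is silent on a limit and does not say when the error is calculated; the gap is inferred from that silence.
- A reader might take the scale wording to admit any coarser instrument. The same sentence names the models, so the sign is loose notation.

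**Conclusion.** The point holds in limited form. Section 7.3 treats weight as sensitive to error and pays for a second observer, but it states no tolerance and no re-weigh, so a gross misread is halved and not corrected. For one child, a misread above 0.70 kg outweighs the planned 0.35 kg, and an unfavourable one above 0.18 kg reverses the expected control gain.

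For the trial, the consequence is lost precision and some misclassification in the secondary outcome: about 7% to 20% more summed variance if random 1 kg misreads affect 1% to 3% of readings, with power for the planned effect essentially unchanged. How many children would be misclassified cannot be computed from the documents. A reader might also infer bias, because staff are not blinded. Section 7.2 acknowledges possible observer bias, but nothing in the documents indicates that misreads would differ between arms.

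The change is worth making because it is cheap and the missed reading cannot be recovered later. The trial does not fail without it.

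**What to change.** Add to section 7.3: the two observers record their readings independently, and the readings are compared before the child leaves. If they differ by more than a pre-set tolerance, both observers weigh the child again, the mean of the two closest readings is used, and all readings are kept. A tolerance of 100 g (five steps of 20 g) is an example only; the sponsor should confirm the value. The rule should apply identically in both arms, so that the decision to re-weigh is not left to staff who may know the allocation.

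The cost is a short addition to the protocol, two spare boxes on the form and about a minute for each child with discordant readings. No extra staff are needed, because both observers are already present.

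Optionally, reword the scale specification to 20 g or finer. This is clerical.

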**7.4 Malaria treatment**

## In order to achieve a similar compliance with malaria treatment in the two study arms, directly observed malaria treatment will be implemented in both groups.

## Children will remain under observation for 30 minutes after treatment to ensure they don’t vomit their medication. If they do vomit the medication within 30 minutes, the same treatment regimen will be given again and children will again remain under observation for 30 minutes.

Parasite clearance will be monitored by blood slide readings on D2. Treatment failure will be assessed on D2, including parasitaemia higher than D0 count. In the case of treatment failure, a 2nd line treatment regimen will be used, as per local MSF treatment protocols. These children will be withdrawn from the study.

**7.5 Laboratory examination and quality control**

Extra training will be given to the laboratory staff about the rationale and methods of the study. MSF standard procedures for laboratory quality control will be applied. Routinely a thick blood film will be taken at D0 (after the result of the paracheck**®** test is positive) D2 and D13.

Blood films will be examined to determine the presence and the density of falciparum parasites. Slide results will be recorded in ‘number of parasites per microlitre (#/µL)’ and further be rated :+ =1-10 parasites per 100 thick film fields

++ =11-100 parasites per 100 thick film fields

+++ =1-10 parasites per single thick film field

++++ = more than 10 parasites per single thick film field

During the first 3 days of the study 20% of blood slides will be reread by a second microscopist. All weak positive slides will be crosschecked. Discrepant results will be assessed and clarified amongst the two available microscopists. All blood slides will be appropriately stored for future external QC; normal MSF quality control procedures will be implemented: 10% of the slides will be referred to a reference lab (PathCare in Nairobi) for cross-checking. This sample of 10% should show 100% agreement. If not, then all slides will be crosschecked.

Haemoglobin levels will only be assessed when anaemia is clinically suspected, as is the current clinical procedure.

# 8. DURATION OF THE STUDY

Training of the staff and pre-testing of the questionnaire (e.g. nurse, measurers, active case finding, laboratory staff) will take 1 week. Participants will be enrolled in 4 weeks (total one month). Follow up will extend for one month after enrolment of the last participant. The final analysis and writing up of reports will take 2 months.

# 9. INVESTIGATORS AND THEIR RESPONSIBILITIES

**9.1. Responsibilities**

The Public Health Department of MSF-OCA is responsible for the study. Only on the authority of the Medical Director or the MoH of DRC should the study be substantially altered or stopped. The principal investigator (PI), [name], is accountable to MSF-OCA.

A scientific advisory committee will advise the PI at crucial stages on design and implementation of the study.and includes:

- The principal investigator
- Members of the Public Health department at HQ levels knowledgeable in research or extensive knowledge of the area;
- The medical responsible in Katanga for MSF-OCA programs (medco) is responsible for input in the research design on issues related to local circumstances, overall organization of the study and all communications with the authorities concerning the study.
- The field research supervisor will be responsible for communication with stakeholders in the community and ensuring the quality of diagnosis, treatment, the completeness of case report forms, follow-up visits and data entry. who is the responsible for field implementation.
- The Médecin Inspecteur Provincial of Katanga is responsible for the government’s commitment to the study, and suggestions to make the study appropriate for the population concerned.
- The Medical Director of MSF-OCA is the final overall responsible;

The research team who are directly involved in the execution of the research consists of the Principle investigator, the medical responsible for MSF–OCA programs in Katanga, the field research supervisor and the medical director MSF OCA.

**9.2. Authorship:** Authors will be drawn from the study groupand will be considered to be **authors** if they have made a substantial personal contribution (in time and effort) to the design, implementation, analysis, and write-up of the study. Other study group members will join the list of **contributors** that will be acknowledged in any publications or presentations.

# 10. RECORDS, DATA PROCESSING & ANALYSIS/REPORTING

**Patient records**

Patient records specific to the study will be kept on the study site and handled confidentially, and will be kept at MSF offices at capital level after follow up for storage. All data (paper records and electronic data) will remain the property of MSF-OCA.

As patients approach the clinic for medical care, standard procedures for patient care will be followed and patient medical cards will remain in possession of the patient (as per current standard procedures in the Dubie health services).

**Data entry**

Data will be entered twice in EpiData/Excel, and analysed in Epi-Info and SPSS.

**Data analysis**

The primary analysis will be aimed at determining the impact of the intervention on mean weight change over the study period. The impact of the intervention will be assessed using multivariate linear regression, with intervention status included as an explanatory variable in a model adjusted for all major confounders identified in previous studies and found to be significant in the primary analysis.

Secondary analyses will include assessing the proportion of children with weight gain post malaria and the impact of intervention on this, and evaluation of factors associated with weight gain at 4 weeks compared to 2 weeks post-intervention.

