# 1. INTRODUCTION

**1.1 The inter-relationship between infection and malnutrition**

The aetiology of malnutrition in most tropical countries is multi-factorial, not only involving an inadequate diet but also recurrent infections.[[1]](#endnote-2) Specifically young children have a high exposure to acute infectious diseases (diarrhoea, acute respiratory infection) and they are at high risk of developing malnutrition. In many countries the situation seems to have worsened in recent years.[[2]](#endnote-3)

Infections are generally associated with weight loss during the illness. This occurs because infections may 1) decrease food intake (anorexia); 2) impair nutrient absorption; 3) cause direct nutrient losses; 4) increase metabolic requirements or catabolic losses; and 5) impair transport of nutrients to target tissues. Fever can account for 20-30% of reduced intake.[[3]](#endnote-4) In addition infections can cause increased losses (malabsorption, diarrhoea) and increased utilisation of nutrients (increased secretion in the gut, internal diversion for metabolic responses, increased metabolic rate when fever is present).[[4]](#endnote-5) As increased needs are not compensated by increased consumption, weight loss during an infection is frequent.[[5]](#endnote-6)

The weight loss occurring during an infection is not equal for all infections. Diarrhoea is known to induce weight loss and studies show that also malaria can result in a large weight loss. [[6]](#endnote-7), [[7]](#endnote-8) Lack of convalescence (i.e. failure to return to normal nutritional status) after an infectious disease makes a child more susceptible to further infections such as diarrhoea and malaria that, in turn, will reduce the nutritional state further. 6,7,[[8]](#endnote-9), [[9]](#endnote-10)

Effects of short-term weight loss during episodes of acute infection can be mitigated by good nutrition allowing for catch up growth.[[10]](#endnote-11),[[11]](#endnote-12) However, recovery of nutritional status is often not complete as good nutrition may be lacking. As a consequence a permanently lower nutritional status is established.[[12]](#endnote-13)

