The sample will be drawn from the group of children who come to the clinic, have been clinically reviewed and are suspected malaria cases. If the malaria rapid diagnostic test is positive, from this group **one in three** child will be selected randomly, and invited to join the study. This selection procedure is necessary as more children will be presenting with malaria then study can process in a day. After explaining the study and the consent procedure, the patient will be randomly allocated to either the control group or the intervention group. The random number function of a pocket calculator will be used for randomisation. In the first step numbers ending on 3,6 and 9 will be invited for the study, numbers ending on 1,2,4,5,7,8, will not be invited, and when a number ends no 0 a new random number will be generated. Numbers ending on an even number or a zero will be in the intervention group, numbers ending on uneven will be in the control group.

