# 5. CONFOUNDING FACTORS

There are many factors potentially influencing weight gain or loss other than a given supplement. These confounders may influence the study outcome. In reviewing previous literature, the following known confounders for convalescence15 or for the relationship between malaria and nutritional status6, 9, [[26]](#endnote-23) will be measured:

- Duration of the complaints before attending the clinic [[27]](#endnote-24)
- Duration of symptoms of malaria before attending the clinic
- Age of child (effect modifier 23); as age may be unreliable length/height can be used as a matched variable
- Breastfeeding (partial, as exclusive breastfed children are excluded)
- Disease history (e.g., respiratory tract infections, diarrhoea, vomiting, anorexia) during the last 2 weeks before enrolment
- Incident diseases during the study period
- Socio-economic status of the family
- Educational status of the caretaker and head of the household
- Maternal age
- Nutritional status at baseline
- Being resident or displaced.

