**6.2 Day 14 after treatment**:

At day 14 a further questionnaire (see annex 4) will be administered, in addition to anthropometry measurements and repeat medical examination:

- Anthropometry: weight, MUAC, oedema
- Medical status: fever, appetite, intercurrent illnesses,
- Laboratory data: thick blood film and level of parasitaemia
- Medical history: duration of symptoms, new illnesses.

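### The primary model's covariate rule admits incident disease, a post-randomisation variable, so part of the RUTF effect could be adjusted away

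*Protocol*

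**What the plan says.** Section 10 (Data analysis) makes regression the primary assessment: "The impact of the intervention will be assessed using multivariate linear regression, with intervention status included as an explanatory variable". The other terms are set by a rule and not by a list, since the treatment term is to be estimated "in a model adjusted for all major confounders identified in previous studies and found to be significant in the primary analysis". The section names no covariates, does not limit them to baseline, and does not name an unadjusted comparison as primary.

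Section 5 is the protocol's only list of literature-based confounders. It opens with "In reviewing previous literature, the following known confounders for convalescence15" (the 15 is a reference number) and has eleven items. Ten describe the child or household at or before enrolment. The other is "Incident diseases during the study period".

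That item is collected during follow-up. Section 6.2 lists, for day 14, "Medical history: duration of symptoms, new illnesses", section 6.3 again records new illnesses at day 28, and Annex 4 asks the caregiver about the preceding two weeks.

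Allocation is random (section 3.3): "Numbers ending on an even number or a zero will be in the intervention group, numbers ending on uneven will be in the control group".

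Section 1.1 supplies both links of a causal chain. Failure to recover nutritionally "makes a child more susceptible to further infections such as diarrhoea and malaria", and "Infections are generally associated with weight loss during the illness".

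**The concern.** With random allocation, an event that happens afterwards cannot confound the comparison of arms. It can be a consequence of allocation. On the protocol's own reasoning, fewer illnesses is one way in which RUTF could raise weight. That route belongs to the effect named in the primary objective, which concerns how far providing RUTF promotes catch-up growth. A model that holds illness constant answers a narrower question and will usually give a smaller figure if RUTF reduces illness.

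The selection rule is a second weakness. Covariates for the primary analysis must be significant in the primary analysis, so the rule presupposes the result that it is meant to define. No threshold or procedure is given. Age and baseline nutritional status, both on the list, stay in the model only if they reach significance. The primary estimate therefore depends on choices made after the data are seen.

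At stake is the estimated size of the effect. The sponsor says it will consider changing its own treatment protocols on the strength of this study (sections 1.3 and 11).

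**Working it through.** **Planning figures (section 3.3).** Mean gain over 14 days is 0.09 kg (SD 0.44) in controls and 0.44 kg (SD 0.33) with RUTF, a difference of 0.35 kg. The stated sample sizes reproduce:

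- Printed formula: 2 × (1.96 × 0.44 / 0.35)² = 12.14, rounded up to 13.
- Unequal variances, 80% power: (0.44² + 0.33²) × (1.96 + 0.8416)² / 0.35² = 19.38, rounded up to 20.
- With 20% loss: 20 × 1.20 = 24.

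The point does not rest on an error in these. The 0.35 kg serves below as the true total effect.

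**Amount removed.** Let p_C and p_R be the proportions of control and RUTF children with an incident illness, and b the weight lost per illness. In a linear model with no interaction, and no unmeasured common cause of illness and growth:

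- total effect = direct effect + (p_C − p_R) × b
- coefficient after adjusting for illness = direct effect
- amount removed = (p_C − p_R) × b

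The protocol gives none of p_C, p_R or b. The values below are assumptions. Each row was also simulated (100 per arm, residual SD 0.4, 1,000 trials), with illness kept if p < 0.05.

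| Illness, control vs RUTF | b (kg) | Removed (kg) | Share of 0.35 kg | Mean estimate without illness | Mean estimate with illness | Trials keeping illness |
|---|---|---|---|---|---|---|
| 40% vs 35% | 0.2 | 0.05 × 0.2 = 0.01 | 2.9% | 0.346 | 0.336 | 92.4% |
| 40% vs 30% | 0.3 | 0.10 × 0.3 = 0.03 | 8.6% | 0.350 | 0.318 | 99.9% |
| 40% vs 20% | 0.3 | 0.20 × 0.3 = 0.06 | 17.1% | 0.354 | 0.293 | 99.3% |
| 60% vs 30% | 0.5 | 0.30 × 0.5 = 0.15 | 42.9% | 0.350 | 0.201 | 100% |

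If p_C = p_R, nothing is removed by this route. If RUTF raised illness, the sign would reverse. The last column applies only if illness is a candidate covariate and costs the assumed weight.

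**Selection rule alone.** Under no treatment effect, with ten baseline covariates explaining 0% or 20% of the variance and 3,000 trials per setting, type I error at a nominal 5% was:

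| Per arm | Variance explained | All covariates fixed in advance | Kept only if significant |
|---|---|---|---|
| 80 | 0% | 4.9% | 5.3% |
| 80 | 20% | 4.6% | 6.0% |
| 100 | 0% | 5.3% | 5.3% |
| 100 | 20% | 4.9% | 5.7% |

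**Effect on the hypothesis test.** With the planning SDs, √(0.44² + 0.33²) = 0.55. At 100 per arm the standard error is 0.55 / √100 = 0.055 kg. An effect reduced to 0.20 kg gives 0.20 / 0.055 = 3.64, and power Φ(3.64 − 1.96) ≈ 95%. At 80 per arm after 20% loss, the standard error is 0.0615 kg, the ratio 3.25, and power about 90%.

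**The case against.** **The link to section 5 is an inference.** The Data analysis section does not cite section 5, and it speaks of major confounders, an undefined subset. Section 5 says its factors will be measured, not that each enters the primary model. The one explicit pointer to that list is under the secondary outcomes in section 4.2. This stands in part: a reader might infer that incident disease will enter the primary model, but the text supports only that it could. The concern survives because no other list exists, the wording of the two places matches, and nothing excludes the item.

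**Mediation may be weak over 14 days.** Section 1.1 does not say that two weeks of supplement would change illness within those same two weeks, and the day-14 recall questions may also pick up the index malaria episode. This stands, and it is why the range must start at zero. The measurement point does not rescue the adjustment, however. Illness is reported by caregivers who know the allocation, so reporting that differs by arm could distort the coefficient even without a true effect on illness.

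**The hypothesis test survives.** At the planned difference this is right. Even the largest assumed loss leaves power of about 90% or more, so the documents do not support reading this as a threat to detecting the planned effect. The harm is to the size of the estimate.

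**The selection rule does little measurable damage, and may only be loosely worded.** A reader might infer serious inflation of type I error, but simulation shows about 5% to 6%. The wording might also mean univariable screening. Either way the model is left to the data.

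**Main outcome as a plain comparison.** Section 4.2 describes comparing group averages. The Data analysis section nevertheless assigns the assessment of impact to the adjusted model.

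**Conclusion.** The point holds as a fault in what the protocol fixes, not as a detail left to an analysis plan. A plan that followed the stated rule could condition the primary estimate on a consequence of treatment, and a plan that avoided this would have to depart from the rule.

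The size is unknown. Under the assumed inputs, RUTF would be understated by 0.01 to 0.15 kg of 0.35 kg (3% to 43%), and by nothing through this route if it does not alter illness. These figures are on the kilogram scale of the sample-size section, whereas section 4.2 states the outcome in g/kg/day. They also rest on a linear model without interaction. Bias from shared causes of illness and growth, or from differential reporting, is not quantified.

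The circular rule matters because it leaves the primary model open, not because it seriously inflates false positives. A reader might also infer that a strong predictor such as sex is wrongly left out of the list. The documents do not show that sex strongly predicts 14-day gain, so including it is optional.

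**What to change.** In section 10, replace the covariate rule with wording to this effect: *The primary model contains allocation and a short set of variables named in advance and measured at or before allocation (for example baseline weight or nutritional status, and age; sex optional). These are kept whether or not they are significant. No variable measured after allocation is included.*

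In section 5, label incident disease as post-randomisation. Analyse it only in the secondary analysis of contributing factors, which already exists as the fourth specific objective in section 2 and as a secondary outcome in section 4.2.

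The cost is one paragraph and one label. All the variables are already collected, and no visits, measurements or participants need to be added. The change should be made before any outcome data are examined.
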